## Abstract

**Background:**

Despite the chronicled success of low-density lipoprotein cholesterol (LDLc)-lowering statin therapy, substantial residual cardiovascular (CV) disease risk remains a problem worldwide, highlighting the need to for combination therapies targeting non-LDLc factors, such as with fenofibrate.

**Methods/design:**

The STAFENO trial is a prospective, randomized, open-label, multi-center trial to compare the effect of statin plus fenofibrate with statin alone on the reduction and stabilization of plaque in non-diabetic, combined dyslipidemia patients with non-intervened, intermediate coronary artery disease (CAD) using virtual histology-intravascular ultrasound at 12 months. A total of 106 eligible patients are planned to be randomized to receive either a combination therapy (rosuvastatin 10 mg plus fenofibrate 160 mg/day) or monotherapy (rosuvastatin 10 mg/day) for 12 months. The primary endpoint of this study is the percentage change in the necrotic core volume. Secondary endpoints include changes in tissue characteristics and 1-year major CV events, including all-cause mortality, CV mortality, nonfatal myocardial infarction, stroke, and revascularization of the intervened and non-intervened lesions.

**Discussion:**

The STAFENO trial will address whether combination treatment of statin and fenofibrate has an additive beneficial effect compared to statin alone on the reduction and stabilization of plaque and CV events in non-diabetic, combined dyslipidemia patients with non-intervened intermediate CAD.

**Trial registration:**

ClinicalTrials.gov, NCT02232360. Registered 9 February 2014.

https://register.clinicaltrials.gov/prs/app/action/SelectProtocol?sid=S0004ULE&selectaction=Edit&uid=U00023SZ&ts=2&cx=juppd2

## Background

Coronary artery disease (CAD) is the leading cause of cardiovascular (CV) disease in developed countries, with approximately 1,350,000 patients presenting with acute coronary syndrome (ACS) annually in the United States alone [1]. Although percutaneous coronary intervention and optimal low-density lipoprotein cholesterol (LDLc)-lowering statin therapy have substantially reduced recurrent CV events in ACS, two-thirds of the CV disease risk remains [2–7]; this highlights the need to redirect the current CV reduction algorithms to focus beyond LDLc reduction and the use of statins [7, 8].

In the 2016 European guidelines for the management of dyslipidemias [9], non-high density lipoprotein cholesterol (non-HDLc) is indicated as a strong independent risk factor and should be a a secondary treatment target (class IIa, level of evidence B). In these guidelines, in high-risk patients with triglyceride (TG) more than 200 mg/dL despite statin treatment, fenofibrate may be considered for use in combination with statins (class IIa, level of evidence B). Although the FIELD and ACCORD trials did not demonstrate favorable efficacy of fenofibrate in diabetic patients, these studies showed that fenofibrate treatment reduced the CV event rate in patients with high TG or low HDLc levels [10, 11]. A meta-analysis of fibrates on CV outcomes also confirmed a significant reduction in CV disease risk without an increase in drug-related adverse events [12]. These data suggest that statin and fenofibrate combination therapy is a potential alternative to statin alone in CAD patients with high levels of non-HDLc. Angiographically, mild atherosclerotic plaques account for 50% of recurrent CV events, further bringing non-culprit vessels into focus as a useful surrogate marker for future CV events [5]. Virtual histology (VH)-intravascular ultrasound (IVUS) allows the tissue characterization and quantitative assessment of plaque, which provides an extensive understanding of the non-culprit lesions [13]. Here, we seek to determine the additive impact of fenofibrate versus optimal statin therapy on non-culprit lesions in non-diabetic, combined dyslipidemia patients with non-intervened intermediate coronary artery disease using well-defined VH-IVUS criteria.

## Methods/design

### Study design and subjects

This is a prospective, open-label, randomized, multi-center trial to investigate the efficacy of statin plus fenofibrate treatment compared to treatment with statin alone in non-diabetic, combined dyslipidemia patients with non-intervened intermediate CAD.

A brief flowchart of the study is summarized in Fig. 1.

**Figure Fig1:**
[figure not shown]
**Fig. 1** A Brief Flowchart of the Study

In non-diabetic patients with suspected CAD, coronary angiography (CAG) will be performed with the standard technique. Percutaneous coronary intervention (PCI) will be performed in culprit lesions based on the decision of an interventionist in participating centers within Korea [14]. Non-culprit lesions (index lesions) with intermediate stenosis (percentage diameter stenosis, 30–60%) by CAG will be evaluated by VH-IVUS if the patients meet the study inclusion and exclusion criteria. Data will be stored for off-line analysis.

Patients will be randomized at ratio of 1:1 using a random table (made by matches of age, sex, presentation of coronary artery disease and sequentially numbered) to receive either rosuvastatin 10 mg plus fenofibrate 160 mg or rosuvastatin 10 mg alone. Study drugs will be administered after the index VH-IVUS. Biochemical laboratory tests (fasting state) will be performed at the time of CAG and followed up at the third month (±2 months) and 12th month (±2 months). Follow-up CAG and VH-IVUS examination will be performed at the 12th month (±2 months). Clinical events will be followed up by office visit or by telephone contact if necessary. Adherence to the study drugs will be checked at every outpatient visit, and the decision to discontinue any of the study drugs will be discussed and checked under the recommendation of the responsible cardiologist. Other drugs which influence lipid profiles will be prohibited during the trial period.

### Study objectives and hypotheses

The primary objective of this study is to compare the changes in percentage necrotic core volume (NCV) and absolute NCV in non-culprit intermediate lesions in non-diabetic, combined dyslipidemia patients after 12 months’ therapy with statin plus fenofibrate compared to statin alone. The working hypothesis of this trial is that statin plus fenofibrate combination therapy is superior to statin alone therapy in reducing the 12-month percentage NCV and the absolute NCV. The secondary objective is to compare changes in percentage and absolute dense calcium (DC), fibrofatty (FF) and fibrous (F) plaques, the incidence of and changes in thin cap fibroatheroma (TCFA), the changes in variables of grey scale IVUS (volumes of external elastic membrane, lumen, and plaque), and the remodeling index between the statin plus fenofibrate and statin alone groups. In addition, secondary endpoints will include comparisons of major adverse cardiac events (MACEs) at 12 months, defined as all-cause death, CV death, nonfatal myocardial infarction (MI), stroke, and ischemia-driven revascularization of intervened and non-intervened lesions between the two groups. In order to identify the mechanisms of plaque stability and regression, the relationships between the variables of the VH-IVUS parameters and laboratory markers, including lipids, inflammatory markers, and metabolic markers, in the statin plus fenofibrate and statin alone groups will be investigated. The incidence of drug adverse effects will be another secondary endpoint of the study.

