#### Study endpoints

The primary endpoint of this study is the comparison of the change in percentage NCV and absolute NCV between statin plus fenofibrate and statin alone groups of non-diabetic, combined dyslipidemia patients with non-intervened intermediate coronary artery disease at 12 months. The secondary endpoints are as follows: 1) comparisons of the changes in other tissue components of percentage and absolute plaque volume in index non-intervened lesions, including DC, FF, and F; 2) change in plaque phenotypes such as TCFA; 3) change in grey IVUS parameters, including vessel area/volume, lumen area/volume, plaque area/volume, and remodeling index; 4) MACEs for 12 months, including all cause death, CV death, nonfatal myocardial infarction, stroke, and ischemia-driven revascularization of intervened and non-intervened lesions; 5) relationships between the changes in tissue components of plaque and changes in laboratory findings; 6) adverse reactions to the study drugs, including myalgia, elevation of CPK more than twice the upper limit of normal, and hepatic dysfunction (alanine aminotransferase more than three times the upper limit of normal).

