### Statistical analyses

The primary endpoint of percentage NCV and absolute NCV will be analyzed using a paired-sample *t*-test or Wilcoxon rank-sum test for changes within each group, and an unpaired *t*-test or Mann–Whitney U test for differences between the two groups. Continuous variables will be expressed as mean ± standard deviation and compared by either a Student’s *t*-test or Mann–Whitney U test based on whether or not the data are normally distributed. Categorical variables will be expressed as number or percentage and compared by χ^2^ or Fisher’s exact test. Pearson correlation test will be used to evaluate the correlation between the changes in percentage NCV and absolute NCV, and changes in laboratory findings from baseline to follow-up. These statistical analyses will be performed in the entire index non-culprit segment and the most severe 10-mm segment centered on the minimal lumen area.

Multivariable linear regression analysis will be performed in order to identify the independent predictors of the reduction in percentage NCV. To analyze the secondary endpoints, VH-IVUS parameters, grey IVUS parameters, and angiographic parameters will be analyzed using a paired sample *t*-test or Wilcoxon rank-sum test for changes within each group, and an unpaired *t*-test or Mann–Whitney U test for differences between the two groups. Correlations between these parameters and laboratory variables will be evaluated by the Pearson correlation test.

Changes in the phenotypes of the index lesions between the two groups will be compared by χ^2^ or Fisher’s exact test. The composite endpoint of CV events will be analyzed by comparing the Kaplan–Meier event rates using a log-rank test. A *p* value < 0.05 will be considered statistically significant.

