## Conclusions

We believe that the STAFENO trial will address whether combination statin plus fenofibrate treatment has additive beneficial effects compared to statin alone on the reduction and stabilization of NCV, and the plausible mechanisms of these results, in non-culprit plaques of non-diabetic patients with combined dyslipidemia.

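### The mechanism objective rests on Pearson tests without randomised arm, pooled or per arm unstated; either choice serves it poorly, and an arm-adjusted model would do better

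*Protocol article*

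**What the plan says.** **Aim.** Study objectives and hypotheses introduces the plaque-laboratory analysis with "In order to identify the mechanisms of plaque stability and regression" and says that relationships between VH-IVUS parameters and lipid, inflammatory and metabolic markers "in the statin plus fenofibrate and statin alone groups will be investigated". Study endpoints lists this as secondary endpoint 5: "relationships between the changes in tissue components of plaque and changes in laboratory findings". The Discussion again says that mechanisms will be sought in direct relationships with marker changes, and the Conclusions promise to address "the plausible mechanisms of these results".

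**Method.** Statistical analyses states: "Pearson correlation test will be used to evaluate the correlation between the changes in percentage NCV and absolute NCV, and changes in laboratory findings". For the other VH-IVUS, grey-scale and angiographic parameters it adds: "Correlations between these parameters and laboratory variables will be evaluated by the Pearson correlation test". The threshold is p < 0.05. The section does not say whether correlations are pooled or run within each arm, and it names no arm term, interaction or between-arm comparison for them.

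**The one multivariable model.** The same section has: "Multivariable linear regression analysis will be performed in order to identify the independent predictors of the reduction in percentage NCV". Its covariates are not listed.

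**The concern.** Treatment is randomised and is expected to move both sides of these correlations. The trial is powered on a fenofibrate effect on percentage necrotic core volume (NCV), and the rationale for choosing fenofibrate describes fibric acid as lowering triglycerides and raising HDLc. A two-variable Pearson coefficient has no place for arm, so the result depends on an unstated choice.

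- **Pooled.** Any marker that the drug shifts becomes correlated with NCV change if the drug also changes NCV, whatever the route. A bystander marker can then be reported as a plausible mechanism.
- **Per arm.** The shift artefact disappears, but each test uses half the patients. A reader shown one significant and one non-significant coefficient has no test of whether the relationship differs.

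What is at stake is the credibility of the mechanism findings, not the primary result.

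**Working it through.** **Inputs from Sample size calculations.** Difference 4.78 in percentage NCV, SD 7.82, two-sided alpha 0.05, power 80%, about 42 evaluable per arm, 20% dropout, 53 per arm.

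**The plan's own figure.** n per arm = 2 × (1.960 + 0.842)² × 7.82² / 4.78² ≈ 42.01. At 42 per arm the normal approximation gives 79.99% power (rounding up gives 43, as does the t-based calculation). With dropout, 42 / 0.8 = 52.5, so 53. The stated approximate 42 and the 53 reproduce. The plan gives no figure for the correlations.

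**Standardised planned effect.** d = 4.78 / 7.82 = 0.611 SD.

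**Assumptions.** Normal data and 42 evaluable per arm. The documents give no correlations or marker shifts, so ranges are used: shifts s of 0.5 to 2 SD and true correlations r of 0.2 to 0.5.

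**Pooled reading (84 patients, no association within either arm).** With 1:1 allocation the absolute size of the induced correlation is

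(s × d / 4) / √[(1 + s²/4)(1 + d²/4)], where 1 + d²/4 = 1.093.

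For s = 1: 0.1528 / √(1.25 × 1.093) = 0.131. For s = 2: 0.3056 / √(2 × 1.093) = 0.207.

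Simulated rates of p < 0.05:

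| Marker shift (SD) | Induced correlation | Pearson, pooled | With arm term |
|---|---|---|---|
| 0.5 | 0.07 | 10% | 5% |
| 1 | 0.13 | 22% | 5% |
| 1.5 | 0.18 | 36% | 5% |
| 2 | 0.21 | 48% | 5% |

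Run within one arm, the same bystander marker is also significant in only about 5% of trials.

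**Per-arm reading (42 per arm, same true r in both arms).** If p is the power in one arm, the chance that only the combination arm is significant is p(1 − p). For r = 0.3 this is 0.50 × 0.50 = 0.25.

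| True r | Power per arm | Only combination arm significant | Power of one arm-adjusted slope |
|---|---|---|---|
| 0.2 | 25% | 19% | 44% |
| 0.3 | 50% | 25% | 80% |
| 0.4 | 76% | 18% | 97% |
| 0.5 | 93% | 6% | over 99% |

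The last column assumes equal slopes in the two arms. The statin-alone arm is the only significant one equally often, so the two p-values disagree in about 37%, 50%, 36% and 12% of trials. A direct between-arm test (Fisher z) declares a difference in about 5%.

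**Limit of a between-arm test.** At 42 per arm, 80% power needs a Fisher z difference of (1.960 + 0.842) × √(2/39) = 0.63, for example a correlation of 0 in one arm against about 0.56 in the other.

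**The case against.** The strongest reply is that much of this rests on silence. Pooling and adjustment of exploratory correlations are often settled in a fuller document. Endpoint 5 as worded asks only for association and contains no arm contrast, and the wording about mechanisms is modest. This keeps the point small but does not remove it. The article does not leave the method open: it names the test, the variables and the threshold for a stated mechanism aim, and the named test cannot carry an arm term.

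Second, the multivariable regression for percentage NCV may include arm, since its covariates are not listed. This stands. It would be wrong to say that arm appears nowhere in the plaque analyses; the absence is certain only for the Pearson tests. But that model does not cover absolute NCV or the other plaque parameters, and it is not named as the mechanism analysis.

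Third, a reader might infer that the investigators will compare arms by which p-value falls below 0.05, or will call a mechanism specific to one arm. No section says so. The per-arm discordance shows only what such a reading would be worth; it is not the error rate of a planned test.

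Fourth, a reader might take both harms to apply together. They cannot: with pooling there are no two p-values to disagree, and within arms the bystander artefact is absent.

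Finally, an arm-adjusted slope shows association within arms, not mediation. This also stands. An equal slope in both arms is compatible with a fenofibrate mechanism, so an interaction cannot be made a condition for every mechanism claim.

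**Conclusion.** The point holds in a limited form. The article fixes unadjusted Pearson tests for a mechanism objective and does not say how the two arms enter, and neither way of running them serves that objective well. Pooled, false association rises from 5% to between 10% and 48% over the assumed shifts, given the full planned NCV effect; the induced correlations themselves are modest, at 0.07 to 0.21. Per arm, the cost is power (50% against 80% at r = 0.3, if slopes are equal), and a contrast drawn from the two p-values would be unreliable, with only the combination arm significant in 6% to 25% of trials when the true correlations are equal. All of these rates depend on assumed correlations or shifts. The aim is secondary, and the primary comparison and sample size are untouched. The change is worth making because it is nearly free.

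**What to change.** For secondary endpoint 5, replace the Pearson tests with one linear model per marker, fitted to both arms together: plaque change on marker change plus randomised arm. Take statements about association from the arm-adjusted slope. Include arm in the existing percentage-NCV regression and say so.

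Add an arm-by-marker-change interaction only where a claim is made that a relationship differs between arms. Keep per-arm correlations as descriptive figures without p-values. Label the results exploratory associations and state that they do not establish mediation.

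The cost is protocol or analysis-plan wording and a few lines of code, with no new data or visits. The small downside is that the interaction has low power at this size, so claims of a difference between arms will seldom be supported.

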### Study population and entry criteria

Inclusion criteria are as follows: (1) age ≥ 20 years; (2) presence of non-culprit intermediate lesions confirmed by index CAG; and (3) combined dyslipidemia (baseline LDLc ≥ 70 mg/dL and non-HDLc ≥ 130 mg/dL in statin-naïve patients, and baseline LDLc ≤ 100 mg/dL and non-HDLc ≥ 100 mg/dL in patients on statin treatment). A non-culprit lesion is defined as a VH-IVUS-feasible native coronary lesion with 30–60% stenosis, 2.0–4.0 mm in diameter by visual estimation during CAG, and located more than 10 mm apart from the intervened lesion.

Exclusion criteria are as follows: (1) diabetic patients; (2) poor cardiac, renal, or hepatic function; (3) explicit side effects and/or contraindications to lipid-lowering agents, including pregnancy, breastfeeding, and familial hypercholesterolemia; (4) very high triglyceridemia (TG ≥ 500 mg/dL); (5) lesions that might cause difficulties for VH-IVUS. Detailed inclusion and exclusion criteria are summarized in Table 1.

**Table 1 Tab1:** Inclusion and exclusion criteria

**Inclusion criteria**	
• Patients with coronary artery disease who were 20 years of age or older and required coronary angiography	
• Patients who require PCI in culprit lesions	
• Intermediate coronary artery stenosis (diameter stenosis ≥ 30% to ≤ 60% by visual estimation, diameter ≥ 2.0 mm to ≤ 4.0 mm, de novo lesion in native coronary artery, more than 10 mm distance from PCI sites) in which virtual histology-intravascular ultrasound (VH-IVUS) is feasible	
• Statin naïve subjects: Combined dyslipidemia (LDLc ≥ 70 mg/dL and non-HDLc ≥ 130 mg/dL)	
• In statin subjects: LDLc ≤ 100 mg and non-HDLc ≥ 100 mg/dL	
• Patients who provided written informed consent	
**Exclusion criteria**	
• Diabetic patients	
• Patients with a history of the use of other lipid-modifying agents (except statins) within the 2 weeks prior to the trial beginning	
• Cardiogenic shock	
• Heart failure with symptoms of New York Heart Association class III/IV or a left ventricular ejection fraction < 35%	
• Renal dysfunction (creatinine level ≥ 1.7 mg/dL) or dependence of dialysis	
• Hepatic dysfunction (transaminase level more than three times that of the normal limit)	
• Pregnancy or breastfeeding women or women of childbearing age	
• Familial hypercholesterolemia	
• Hypertriglyceridemia (triglyceride level > 500 mg/dL)	
• Lesions that might cause difficulties for VH-IVUS due to the following reasons: heavy calcification (> 90° arc), tortuous vessel with severe angulation, total occlusion, or major bifurcation lesions (side branch diameter > 2 mm)	
• Inability to take adequate antiplatelet therapy (aspirin, clopidogrel, ticagrelor, or prasugrel)	
• Thrombocytopenia (platelet count < 70 × 10^9^/L)	
• History of significant arrhythmia including ventricular tachyarrhythmia	
• Familial hypercholesterolemia	

### Randomization, interventions, and data assessment

The schedule of enrolment, interventions, and assessments is outlined in Fig. 2.

**Fig. 2 Fig2:**
[figure not shown]
Schedule of enrolment, interventions, and assessments

Written informed consent for subjects who meet clinical and angiographic inclusion and exclusion criteria will be obtained by an investigator. Personal information is planned to be corrected by interview and chart review. All personal information will be protected by an encoding process. Potential participants are informed of the purpose of the study, the potential hazards and risks, the potential benefits, the procedure, and the expected follow-up after intervention. They are informed that participation is voluntary and that withdrawal from the study may occur at any time. On the consent form, participants will be asked if they agree to the use of their data should they choose to withdraw from the trial. Participants will also be asked for permission for the research team to share relevant data with people from the universities taking part in the research or from regulatory authorities, where relevant. This trial involves collecting biological specimens for storage. Additional permission for storage and measurement of biological specimens will be acquired from participants according to the local IRB’s requests.

After the subjects are enrolled in the present study, subjects will be randomized to two groups using a random box table made by stratified randomization according to subjects’ age, sex, and clinical presentation (acute coronary syndrome or not).

### Research materials

#### VH-IVUS and quantitative coronary angiography

VH-IVUS using a synthetic-aperture-array, 20-MHz, 3.2-French catheter (Eagle Eye, In-Vision gold, Volcano Corp, rancho Cordova, CA, USA) with motorized catheter pullback (0.5 mm per second) after intracoronary administration of nitroglycerin 0.2 mg will be performed in non-culprit lesions with intermediate stenosis. During pullback, grayscale IVUS is recorded and raw radiofrequency data are captured at the top of the R wave for the reconstruction of the color-coded map by a VH-IVUS data recorder (Volcano Therapeutics). Enrolled lesions will be native vessels and should be located more than 10 mm apart from the intervened lesion. Cases where the patients’ condition is unstable or the characteristics of the lesions make it difficult to perform VH-IVUS in terms of severe angulated lesions, calcified lesions, or thrombus containing lesions, will be excluded.

Data from the VH-IVUS and CAG will be measured by an independent investigator who is blinded to patient group and characteristics. Data from VH-IVUS, such as percentage and absolute NCV, DC volume, F volume, FF volume, and presence of thin cap fibroatheroma (TCFA), and data for the gray IVUS, such as external elastic membrane, lumen, plaque volume, and the remodeling index, will be measured in the entire index segment and the most severe 10 mm segment centered on the minimal lumen area at baseline and after 12 months.

Data from CAG, such as reference vessel diameter, minimal lumen diameter, and lesion lengths, will be measured by a dedicated quantitative coronary angiography (QCA) program.

